### Expected loss rate (less than 20%)

The expected loss includes all patient data excluded from the main analysis, usually because of a serious breach of the study protocol by the principal investigator (affecting the evaluation of the primary endpoint of effectiveness). Possible such breaches include failure to meet the inclusion/exclusion criteria; failure to follow the prescribed schedule; follow-up visits not occurring within the specified time limits, and concomitant treatments that may affect incidence of rupture. However, excellent clinical follow-up may achieve a drop-out rate of as little as 5%.

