
## Methods and design

The Study on a Multidimensional Model for Predicting Risk of Rupture of Unruptured Intracranial Aneurysms (CIAP-2) is the second project of the China Intracranial Aneurysm Program and is managed by Beijing Neurosurgical Institute and Beijing Tiantan Hospital), which manages a prospective observational registry of patients with UIA who were enrolled in our 20 centers in China during the first CIAP. It is sponsored by the National Key Research Development Program of China. This study has been designed as a prospective, observational registry and the treatment of patients will not be influenced by their participation in this observational study. This study adheres to the ethical principles of the Declaration of Helsinki and Human Biomedical Research Ethical Issues and Policy Guidance. The Institutional Review Board of Beijing Tiantan Hospital, Capital Medical University has approved the study (KY2017-017-01). We will inform participating patients or their relatives that the privacy of their data will be protected. These know they can withdraw from the study at any time. The study has been registered at https://clinicaltrials.gov/ct2/show/NCT03133624.

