## Statistical methods

### Total sample size

CIAP-1: Calculation of the required sample size using an expected annual rupture rate of 1%, allowable error of d = 0.6%, and alpha = 0.05 on two-sided testing indicated that 1173 patients need to be enrolled per year, that is, 4692 over 4 years. An annual rupture rate of 1% [2] results in a loss rate of less than 20%. A reported hemodynamic index (complex flow patterns OR = 4.7) and HRMRI index (aneurysmal wall enhancement OR = 3.05 for ruptured versus unruptured aneurysm) also indicate that this sample size would be sufficient [12, 43]. Given that genetic factors have not yet been evaluated [35], our genetic testing will assess previously reported possible genetic indicators of prognosis; additionally, target genes and biomarkers will be selected according to the latest research progress in the future. In the 5th year of the study, we will analyze the data. As previously mentioned, at least 130 aneurysms are expected to rupture in the modeling group in the first 4 years. Allowing for a loss rate of 20%, the study will need to enroll 500 individuals.

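### Excluding patients from the main analysis for off-schedule visits or concomitant treatment selects on post-enrolment events: absolute rupture risk is likely to be overestimated, and odds ratios may be biased

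*Protocol article*

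**What the plan says.** Under *Expected loss rate (less than 20%)*, the protocol article defines loss as removal from the analysis and not only as loss of contact: "The expected loss includes all patient data excluded from the main analysis, usually because of a serious breach of the study protocol". The breaches it gives as possible examples are ineligibility, not keeping to the schedule, and "follow-up visits not occurring within the specified time limits, and concomitant treatments that may affect incidence of rupture". Only ineligibility can be judged at baseline.

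Three other places bear on this:

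- *Methods and design*: "the treatment of patients will not be influenced by their participation in this observational study".
- *Data collection and management*: visits are due at 90 ± 14, 180 ± 30 and 365 ± 30 days and then at least annually, and participation stops at rupture.
- *Evaluation of risk factors for aneurysms*: odds ratios come from multiple regression. No time-to-event step and no censoring rule is given.

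The same loss figure feeds the sample size: "Allowing for a loss rate of 20%, the study will need to enroll 500 individuals". A best case is also mentioned: "excellent clinical follow-up may achieve a drop-out rate of as little as 5"%.

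**The concern.** The rule resembles a per-protocol exclusion from a treatment trial, but this study tests no treatment. It aims to estimate who ruptures and with what probability. Two mechanisms matter.

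**Time at risk of exclusion.** A patient who ruptures leaves the study and can no longer miss a window or start a treatment. A patient who does not rupture can do either for the whole follow-up. Exclusion therefore falls more on the unruptured and pushes the estimated absolute risk up, even when it has nothing to do with any predictor.

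**Treatment that follows risk.** Treatment is uncontrolled, and the article names this ground by its effect on rupture. If patients with a suspected risk factor are treated more often, unruptured carriers of that factor are removed preferentially, and the odds ratio for the factor is distorted.

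The output of a prediction model is an absolute risk, so the first mechanism goes directly to the product. The validation group comes from the same cohort. If the same exclusions apply there, validation would not show the problem.

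**Working it through.** **The plan's own figures.** The article does not show how 500 was reached. One route that nearly matches, and is inferred here, takes 130 ruptures with the 1:2 rupture to non-rupture ratio: 130 × 3 = 390, and 390 / 0.80 = 488, within 3% of 500. The 130 itself follows from 5000 × 2/3 × 4% = 133, or 131 with 1 − 0.99⁴ = 3.94%, with no loss applied. A 20% loss spread evenly leaves about 107 or 105. The 20% allowance in the 500 replaces numbers; it cannot correct for who is removed.

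**Inputs for the bias illustration.**

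- From the article: annual rupture rate about 1%; 4 years; effect size 3.05 (the figure quoted for wall enhancement, used here as a hazard ratio); loss up to 20%, or 5% at best.
- Assumed, not in the article: factor prevalence 30%; constant rates; treatment rates chosen so that about 19% are excluded.

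Rupture rate without the factor: 0.01 / (0.7 + 0.3 × 3.05) = 0.00619 per year. With the factor: 3.05 × 0.00619 = 0.01889.

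**Truth without exclusion.** Four-year risks are 1 − exp(−4 × 0.00619) = 2.45% and 1 − exp(−4 × 0.01889) = 7.28%. Overall: 0.7 × 2.45% + 0.3 × 7.28% = 3.9%. Odds ratio: (e^0.0755 − 1)/(e^0.0248 − 1) = 3.13.

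**With treated patients excluded.** For rupture rate h and treatment rate g:

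- rupture first: h/(h+g) × (1 − exp(−4(h+g)))
- neither: exp(−4(h+g))
- everyone else is treated first and removed.

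| Scenario | g with / without factor | Excluded | Rupture first, with / without | Neither, with / without | Overall 4-year risk | Odds ratio |
|---|---|---|---|---|---|---|
| Treatment unrelated to factor | 0.055 / 0.055 | 19.4% | 0.0654 / 0.0220 | 0.744 / 0.783 | 4.3% | 3.13 |
| Treatment follows factor | 0.14 / 0.026 | 19.3% | 0.0559 / 0.0232 | 0.530 / 0.879 | 4.1% | 3.99 |

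In the second row the odds ratio is (0.0559/0.530)/(0.0232/0.879), and the risk in patients with the factor is 0.0559/(0.0559 + 0.530) = 9.5% against a true 7.3%. A simulation of 4 million patients agrees (4.3% in the first row; odds ratio 3.97 in the second). Keeping the treated patients and censoring them at treatment gave a rate ratio of 3.03 in the second scenario, against a true 3.05.

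**Range, by 2×2 arithmetic.** Take a true odds ratio of 3.05 and multiply it by the ratio of retention probabilities:

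- About 5% excluded, unruptured only (12% with the factor, 2.5% without): 3.05 × 0.975/0.88 = 3.4.
- About 19% excluded (unruptured: 45% with, 10% without; no ruptures dropped): 3.05 × 0.90/0.55 = 5.0.
- About 20% excluded, with ruptured carriers dropped more often (40% against 20% for all others): 3.05 × 0.60/0.80 = 2.3, and overall risk falls from 4.0% to 3.5%.
- 20% excluded at random: no change.

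**The case against.** **The text is hedged.** It speaks of serious breaches, says usually, and gives possible examples. A reader might infer that known ruptures will be thrown away because a visit was late. The article does not say that: a rupture found at a late visit need not count as a breach that prevents evaluation of the endpoint. The wording permits such exclusions but does not prescribe each one.

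**The passage explains a sample-size allowance.** The definition of analysis sets commonly belongs in the full protocol or analysis plan, and the statistical methods paragraphs state no exclusion. That is fair, but the article does state who leaves the main analysis, and nothing else in it keeps or censors those patients. The point concerns a rule that is stated, not one that is absent.

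**Concomitant treatment may mean drugs.** The article does not say that aneurysm repair is included, nor does it exclude it. On either reading the ground arises after enrolment and is named for its effect on the outcome. The visit-timing grounds do not depend on this reading, although a link between late visits and baseline risk factors is plausible rather than stated.

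**The distortion could be read as larger than it is.** With assumed rupture rates of 3% and 0.5% per year and repair at 30% and 3% per year, the same formulas give an odds ratio of 11.6 against a true 6.3. That scenario removes 67% of the high-risk patients and 11% of the others, so it fits a loss below 20% only if at most about 16% of patients are high risk: (0.20 − 0.112)/(0.666 − 0.112) = 0.159. It cannot fit a 5% loss. The documents do not support it as the expected size.

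**Conclusion.** The concern stands in a bounded form. As written, the section permits exclusion from the main analysis on events after enrolment. Because rupture ends participation, that removal falls more readily on unruptured patients, so overestimated absolute risk is the likely direction: 3.9% to 4.3% over 4 years at about 19% exclusion, under the assumed rates.

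Odds ratios may be biased but need not be. They are unchanged if treatment is unrelated to the factor, move from about 3.1 to about 4.0 if treatment follows it at about 19% exclusion, and from 3.05 to about 3.4 at about 5% differential exclusion. A reader might infer that the risk estimates will certainly be biased, and always upward. The documents do not support that: the exclusion patterns are not stated, and dropping ruptured carriers more often would lower both measures. All sizes rest on the assumed 30% prevalence, constant rates and treatment patterns.

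**What to change.** - Remove visit timing, schedule deviations and concomitant treatment as grounds for exclusion from the main analysis. Exclude only patients found ineligible on baseline data.
- Use actual visit dates and count every known rupture.
- Analyse time from enrolment to rupture, with analysis follow-up censored at aneurysm repair, death or last contact. Alternatively, treat repair as a competing event. State which is meant: censoring targets the risk if repair did not occur, and the competing-event version the risk under prevailing repair practice.
- Keep the per-schedule set as a sensitivity analysis only.
- Optional check: inverse-probability-of-censoring weights, since censoring at repair recovers the true ratio only if the model holds the factors that drive repair.

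The cost is modest. The follow-up items listed under *Data collection and management* do not name the date of repair, so it must be confirmed as a recorded field. A time-to-event model, or a nested comparison that accounts for time at risk, replaces the plain odds-ratio regression. Patient care and visit schedules are untouched.

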### Statistical analysis methods

#### Statistical analysis of clinical data

Continuous variables will be expressed as mean and standard deviation analyzed by one-way anova. Categorical variables will be expressed as quantity (rate) and compared using χ^2^ tests. Continuous variables that are not normally distributed will be expressed as medians and quantile intervals and compared using the Mann–Whitney nonparametric test. P < 0.05 will denote a significant difference.

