**Methods:**

The China Intracranial Aneurysm Project-2 (CIAP-2) will comprise screening of a cohort of 500 patients with UIA (From CIAP-1) and focus on hemodynamic factors, high resolution magnetic resonance imaging (HRMRI) findings, genetic factors, and biomarkers. Possible risk factors for rupture of UIA, including genetic factors, biomarkers, HRMRI, and hemodynamic factors, will be analyzed. The first project of the China Intracranial Aneurysm Project (CIAP-1; chaired by the Department of Neurosurgery, Tangdu Hospital, Fourth Military Medical University, Xi’an, Shaanxi, China) will prospectively collect a cohort of 5000 patients with UIA from 20 centers in China, and collect baseline information for each patient. Multidimensional data will be acquired in follow-up assessments. Statistically significant clinical features in the UIA cohort will also be analyzed and integrated into the model for predicting risk of UIA rupture. After the model has been set up, the resultant evidence-based prediction will provide a preliminary theoretical basis for treating aneurysms at high risk of rupture.

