### Model building (first set of UIA queues)

The following possible or established risk factors for UIA will be collected and analyzed: age; sex; blood pressure, smoking, alcohol consumption, hyperlipidemia, diabetes mellitus, and family history of subarachnoid hemorrhage, intracranial aneurysm, and autosomal dominant diseases (polycystic kidney, Marfan syndrome, collagen dysplasia, etc.)The following imaging data will be collected and analyzed: shape, location, size, aspect ratio and odds ratio of aneurysms, morphological factors such as the angle of the aneurysm jet, and known risk factors for rupture.In our experience, follow-up angiography alone does not adequately predict the outcome whereas HRMRI is a more useful means of following these lesions [38]. We have also found and reported that aneurysm wall enhancement on HRMRI predicts instability of an intracranial aneurysm [39]. HRMRI will be performed on patients enrolled in the UIA follow-up cohort at the 20 participating centers and HRMRI-identified aneurysm wall enhancement assessed as a possible predictor of UIA rupture. Two-dimensional short-axis images of the aneurysms generated from the registered pre-and post-contrast T1w-SPACE images will be used to identify wall enhancement [13].To identify risk factors, the nested cohort study will incorporate the following: incidence of aneurysm rupture in the follow-up cohort, the definition of UIA recently rupture before the duration of follow-up was high risk of rupture of UIA, acquisition of imaging data for hemodynamic calculations; according to the aneurysm ratio of 1:2 UIA (rupture vs non-rupture), and analysis of differences in hemodynamic variables, genetic factors, and biomarkers.A.Analysis of hemodynamic variables: A three-dimensional shape will be created and image data from computed tomographic angiography, magnetic resonance angiography, or DSA saved as DICOM files. Once the 3D model has been reconstructed, it will be saved in an STL file format. A rigid wall in the parent vessel and aneurysm will be assumed in the simulation of hemodynamics. We will start by using ANSYS ICEM CFD (Materialise, Leuven, Belgium) to build a finite element model, then perform a simulation on ANSYS CFX software (Materialise), and finally use ANSYS CFX POST postprocessing to calculate Wall Shear Stress (WSS), maximum wall shear stress (WSSmax), low WSS areas, steady state of blood flow, and so on. Our team has already identified that these factors are associated with the stability of aneurysms [40–42].B.Gene and biomarker analysis: Blood samples will be collected from all participants and specimens of the aneurysm wall from patients who undergo craniotomy. Target chromosomes will be tested for blindly. Target genes and biomarkers identified as possibly relevant by the latest international research will be tested. Differences in genes and biomarkers between rupture and non-rupture groups will be compared to identify rupture-related factors.

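### The named group tests (one-way ANOVA, and χ² with no sparse-cell exception) are sensitive to unequal SDs at about 130 vs 3203 and to very rare factors; Welch and an exact or mid-P test would protect the P values used to select factors

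*Protocol article*

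**What the plan says.** In the protocol article, the section Statistical analysis of clinical data names the tests:

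- Continuous variables: "Continuous variables will be expressed as mean and standard deviation analyzed by one-way anova".
- Non-normal continuous variables: "Continuous variables that are not normally distributed will be expressed as medians and quantile intervals and compared using the Mann–Whitney nonparametric test".
- Categorical variables: "Categorical variables will be expressed as quantity (rate) and compared using χ^2^ tests".
- Threshold: "P < 0.05 will denote a significant difference".

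Non-normality therefore has a fallback. Unequal variance and small expected counts have none.

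The Design section says that the modeling group is used to compare ruptured with non-ruptured patients and that the factors found go into the model. The abstract says the same of clinical features: "Statistically significant clinical features in the UIA cohort will also be analyzed and integrated into the model for predicting risk of UIA rupture". The candidate list under Model building includes family history of "autosomal dominant diseases (polycystic kidney, Marfan syndrome, collagen dysplasia, etc" and similar conditions, and the same section adds target genes. Hemodynamic variables, genes and biomarkers are compared in a nested set at one rupture to two non-ruptures.

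**The concern.** The cohort-wide comparison sets a small rupture group against a very large non-rupture group. A pooled-variance test then takes its standard error almost wholly from the large group, while the uncertainty in the mean difference comes almost wholly from the small one. If the rupture group is more variable, the test rejects too often. If it is less variable, the test rejects too rarely and real differences can be missed.

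The χ² test relies on a large-sample approximation. For a condition carried by a handful of patients, the expected number among ruptures can be below one, and a single ruptured carrier can pass the 0.05 threshold.

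Because significance decides which features are taken forward, either effect could put a factor into the model or keep one out. This is separate from the number of factors screened: it concerns the accuracy of each P value.

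**Working it through.** **Group sizes.** Inputs: cohort 5000 (abstract), modeling:validation split 2:1 and annual rupture rate 1% (Design), at least 130 ruptures in the modeling group in 4 years (Total sample size).

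- Modeling group: 5000 × 2/3 = 3333.
- The article's 130, reproduced: 3333 × 0.01 × 4 = 133 with no loss applied. With 20% loss it would be 107.
- Non-ruptures: 3333 − 130 = 3203, a ratio of about 1:25.
- Nested comparison at 1:2: 130 vs 260.

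**ANOVA with two groups.** This is the pooled-variance t test. Let r be the rupture/non-rupture SD ratio, with the non-rupture SD set to 1. The article gives no SDs, so every r is an assumption.

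- Pooled variance: s² = [(n1 − 1)r² + (n2 − 1)] / (n1 + n2 − 2).
- Standard error the test uses: A = √[s²(1/n1 + 1/n2)].
- True standard error: B = √(r²/n1 + 1/n2).
- Two-sided type I error ≈ 2[1 − Φ(c·A/B)], where c is the 5% critical value.

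Example, 130 vs 3203, r = 1.25:

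- s² = (129 × 1.5625 + 3202)/3331 = 1.022
- A = √(1.022 × 0.0080045) = 0.0904
- B = √(1.5625/130 + 1/3203) = 0.1110
- A/B = 0.814; c·A/B = 1.961 × 0.814 = 1.597; error = 11.0%

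| SD ratio (assumed) | ANOVA, 130 vs 3203 | ANOVA, 130 vs 260 |
|---|---|---|
| 0.67 | 0.5% | 2.5% |
| 0.8 | 1.6% | 3.4% |
| 1.0 | 5.0% | 4.9% |
| 1.1 | 7.3% | 5.7% |
| 1.25 | 11.0% | 6.8% |
| 1.5 | 17.6% | 8.4% |

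Simulation (4000 normal data sets per setting, ratios 0.67, 0.8, 1.0, 1.25, 1.5) agrees. At 130 vs 3203 ANOVA gave 0.6%, 1.4%, 5.2%, 11.4% and 16.6%, and Welch gave 4.4% to 5.2%. At 130 vs 260 ANOVA gave 2.8%, 3.7%, 5.5%, 6.8% and 8.6%, and Welch gave 4.8% to 5.5%.

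**χ² at fixed carrier counts, 130 ruptures among 3333.** Take 4 carriers, one of whom ruptures.

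- Expected ruptured carriers: 4 × 130/3333 = 0.16.
- Uncorrected statistic: 3333 × (1 × 3200 − 3 × 129)² / (130 × 3203 × 4 × 3329) = 4.76, so P = 0.029.
- Exact probability of at least one ruptured carrier: 1 − 0.853 = 0.147.
- Mid-P: 0.147 − 0.139/2 = 0.078, where 0.139 is the probability of exactly one.

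Uncorrected χ² error under no association moves in a sawtooth: 11.3% at 3 carriers, 14.7% at 4, 1.4% at 5, 2.0% at 6, 3.6% at 8, 10.1% at 14, 1.9% at 15. Over 1 to 30 carriers Fisher's test never exceeds 4.6%.

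**χ² in the nested set, 130 among 390.** With 2 carriers, both ruptured, the exact probability is (130 × 129)/(390 × 389) = 0.111, against an uncorrected P of 0.045.

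**χ² averaged over random carrier counts (prevalences assumed).**

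- 130 vs 3203: 5.8% at prevalence 0.05%, 7.7% at 0.1%, 5.2% at 0.2%, and 3.9% to 4.9% from 0.5% to 10%.
- 130 vs 260: never above 5.0%.
- Fisher, 130 vs 3203: 1.2% to 4.2%.

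**The case against.** The strongest reply is that nothing in the article is shown to go wrong.

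- **ANOVA.** Imbalance alone does no harm: at equal SDs the error is 5.0%. Every distorted figure needs an SD ratio that the article does not supply. Non-normal variables already go to Mann–Whitney. All of this stands, and it makes the point conditional. It does not make the test safe, because the article gives no ground for assuming equal SDs either, and a 10% difference already moves the error to about 7%.
- **χ².** The striking examples sit at peaks of a sawtooth; one more carrier takes 14.7% down to 1.4%. The averaged error is near nominal. No variant is named, and with Yates' correction the two examples above give P = 0.37 and 0.21. The listed disorders may also be analysed as one family-history item. This stands as a limit on size. Still, the analyst will face one realised count, not the average.
- **Later steps.** Multiple regression and validation follow, so these P values are not the only filter. That stands.
- **SAP detail.** Test variants are often settled in a statistical analysis plan, which is not shown. That lowers the severity. But the article does name its tests, so the point concerns a stated choice and not an omission.

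A reader might infer that the 1:25 imbalance makes the named tests give false P values throughout. The documents do not support that: unequal SDs or particular low carrier counts are needed, and hemodynamic, genetic and biomarker comparisons are at 1:2.

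**Conclusion.** The point holds in conditional form and at modest severity. In the cohort-wide modeling comparison the named ANOVA, read in its ordinary pooled form, depends on equal SDs: its error runs from about 1.5% to 17% as the assumed SD ratio goes from 0.8 to 1.5, while Welch's test stays near 5%. At 1:2 the range is about 3% to 9%. Uncorrected χ² can understate P several-fold for particular carrier counts of very rare factors, but is near nominal on average and does not exceed 5% on average at 1:2.

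This rests on four assumptions: clinical and imaging features are compared across the whole modeling group; 130 ruptures occur as the article expects; the SD ratios and prevalences are illustrative; and χ² is applied without correction. The documents do not show that any particular factor will be wrongly selected or missed.

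**What to change.** In Statistical analysis of clinical data:

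1. Replace one-way ANOVA with Welch's unequal-variance test for the two-group comparisons of rupture with non-rupture.
2. Keep χ² where all expected counts are at least 5. When any expected count is below 5, use an exact test, preferably in its mid-P form, otherwise Fisher's. Name one in advance.

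The cost is two sentences and standard software options, with no new data. Welch holds its level at equal SDs as well, so the change does not depend on knowing the ratio. Fisher's test is conservative for very rare factors (1.2% to 4.2% at 130 vs 3203). Mid-P is less so, at the price of a slight excess at isolated counts: with 2 carriers, one ruptured, the exact P is 0.0765 and the mid-P is 0.0015 + 0.075/2 = 0.039, so it would reject 7.65% of the time at that count.
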